#### **11.3.2.2. New fact reporting**

When a new event is likely to affect the safety of participants, the sponsor and the investigator take appropriate urgent safety measures to protect participants against any immediate hazard.

The sponsor inform without delay the Ethic Committee and DSMB of safety data that may be relevant in terms of subject safety, or safety issues which might alter the current benefit-risk assessment of the trial.

The safety office shall transmit a written report, within 15 days to the applicable Competent Authority and DSMB.

If the new fact requires substantial amendments, the sponsor should notify any substantial protocol modification, to the National Competent Authority and the concerned Ethic Committee, within 15 days of the safety measures implementation.

#### **11.3.2.3. Annual safety reporting**

Once a year throughout the clinical trial, the sponsor should submit to the DSMB (at demand), principal investigator, project leader, international project leader and the Ethics Committee, an annual safety report.

The annual safety report may be submitted to the coordinating investigator for approval.

The annual safety report should be submitted no later than 60 calendar days from the first patient inclusion to conduct the clinical trial in any country.

## Appendix or Figure x : AE Notification

[figure not shown]

## 12. TRIAL BOARDS AND COMMITTEES

### 12.1 Trial scientific committee

#### Composition

The trial scientific committee will consist of: (i) the investigators, the clinical coordinators and statisticians/methodologists of the trial; (ii) the virologists; (iii) a representative of the communicable disease department of the Ministry of Health; (iv) other external experts; and (v) sponsor representatives. Members of the scientific committee are listed in annex 1.

#### Meeting agenda

The trial scientific committee will meet before the beginning of the inclusion phase, as well as once or twice per year until the end of the trial. The trial sponsor or one or several board members may also request a special meeting at any time.

#### Role

The role of the trial scientific committee is to ensure that the trial is carried out appropriately, not only scientifically but also clinically and ethically. The members of the scientific committee report directly to the sponsor.

- They will ensure that the trial personnel carry out the trial properly, adhere to the trial protocol and maintain patient safety;
- They will guarantee that the trial remains scientifically relevant by ensuring the relevancy of the trial questions and that the methods used are valid and appropriate;
- They will make all decisions regarding necessary and relevant protocol modifications, such as:
  - Actions needed to facilitate patient recruitment;
  - Decisions to open or close participating trial sites.
- They will enforce the rules pertaining to access to the trial data as well as reports and publications of the results;
- They will remain in contact with the sponsor, the DSMB and the coordinating investigators, and will make sure investigators and other trial personnel have access to up-to-date information.

At the end of each meeting, a report containing the meeting minutes, signed by the Scientific Committee chair will be sent to the members of the scientific committee, DSMB Members and the director of ANRS EID.

### 12.2 Data Safety & Monitoring Board (DSMB)

#### Composition

The DSMB members will be selected in collaboration between the coordinating investigators and the ANRS EID before the beginning of the inclusion phase.

#### Meeting agenda

The DSMB will meet once at the beginning of the inclusion phase, and at least every 12 months until the end of the trial. The sponsor, the scientific committee or the DSMB may request to increase the frequency of these meetings.

## **Role**

The DSMB is a consultative board for the scientific committee and to the sponsor. Its members will provide general advice on the progress of the trial, including the rate of inclusions, the quality of follow-up, the overall rate of drug-related adverse events, changes in biological markers, the overall incidence of primary outcomes, and the number of subjects needed.

They will help to make difficult decisions that require an independent assessment while the trial is underway. Advice may be needed regarding:

- Premature discontinuation of the trial (because the rate of adverse events is high, the trial is no longer feasible, or the available data are sufficient);
- Substantial changes to the protocol that becomes necessary during the inclusion or follow-up phases, or to account for new scientific information.

The DSMB will conduct and interpret intermediate analyses, if any.

At the end of each meeting, a written report containing the DSMB's opinion will be sent to the sponsor and the members of the scientific committee.

## **12.3 Decision Support Committee (DSC)**

### **Roles of the DSC**

The DSC will provide advices and recommendations to investigators regarding:

- Occurrence of liver adverse event
- Any morbidity event occurring during the study
- Decision on DAA management
- Any important clinical issue for which the investigators wish to share experience before taking a decision

### **Composition of the DSC**

The DSC will consist of 1/ Two physicians specialized in HCV infection 2/ One virologist 3/ The two principal investigators of the study. Other specialists could be called at DSC's request.

### **Organization of the DSC**

The DSC will meet regularly and must be accessible on rapid request through phone calls, e-mails, private online forum, or any other means in case of morbidity event.

The investigators of each site will be responsible to prepare the documents for the meeting and to send it by e-mail at least two days before the meeting.

The responsibility of DSC is to provide a recommendation on a written document. One member of the DSC will be in charge of the written report. This report will be send to the methodological centre in UHS.

## 13. COORDINATION, MONITORING, DATA MANAGEMENT

### Coordination

The UHS Research Grant Management Office is the referent for the trial methodology and management. The UHS team is responsible, in coordination with the clinical, laboratory and administrative coordinators, for the overall trial management (preparation and organisation of the trial, monitoring, data management and analysis). The team will include the clinical coordinators, the statistician, the clinical research assistants, one Lab technician and one data manager.

- **Preparation and organisation of the trial**: the UHS team will finalize and review the Case Report Forms (CRF) with all the collaborators, prepare the recruitment procedures, and organize the trial reference documentation. The MDMC team and the clinical coordination team will prepare the operation manual describing in details the trial procedures for each collaborators (clinical and laboratory activities, treatment dispensation, data management).
- **Database**: The trial database will be developed and maintained by the MDMC in collaboration with NCHADS Data Management Unit. The data manager will also be in charge of the data entry and implementation of data quality insurance plans. H/She has to prepare daily monitoring reports and the data file necessary for the trial analysis.
- **Data analysis and analysis report**: will be coordinated at the UHS MDMC.
- **Reporting**: the operational team will be responsible for finalizing:
  - the necessary reports and presentations for the Scientific Advisory Board and the DSMB meetings;
  - the trial yearly progress reports; The operational team will bring its support in preparing any communications on the trial (poster, oral presentation, papers).

### Trial documents

Essential trial documents will be retained at the MDMC for 15 years. Data will be kept on a secured database installed on a server at the MDMC centre.

### Data management

#### 1.1.1 Data collection

##### Screening phase

E-CRF in Khmer language with the patient code of participants for both arms (Community and facility arms) will be used to collect data of the participant in this study. For that purpose, tablets will be given to community workers and nurses. Each community worker for community arm and each health centre for facility arm will get his own tablet. Data will be collected in household for community arm and in health centre for facility arm. At the end of each day, for community arm, community workers will be in charge to return the tablets in referral health centre. Tablets will be stored in a secured cupboard.

## Treatment phase

CRF paper in English/Khmer language with the patient code of participants will be used to collect data of the participants. Data will be collected during each consultation in the Provincial Hospital.

The CRA from the MDMC will come on a regular basis to check for completeness, accuracy and legibility of data reported on the CRF. He/she will bring back the validated CRF to the MDMC for data entry.

### **1.1.2 Data entry and checking**

Data will be entered at the MDMC (UHS). The trial database will be developed by a database developer; he will closely work with the coordination team.

After entry, the database will be checked for consistency. If any inconsistency or question on the data, the CRA will go back to the clinical monitors at sites for clarification during their monitoring visit. The corrections will be entered and followed in the data base.

### **Data protection and confidentiality**

All the collected patient data will be strictly confidential and coded.

Only persons mandated by the sponsor and involved in the study management and health authorities are able to access to medical files of patients in order to check the accuracy of the collected data.

In order to respect patient confidentiality, each subject who accepts to participate in the study will be allocated a unique identifying code, which is composed of arm, village code, household code and participant code: |\_| / |\_|\_| / |\_|\_|\_| / |\_|\_|\_|\_| (Arm / Village / HH / participant).

Only the code of the subject will be reported in the Case Report Form (CRF).

The trial data will be recorded and be managed informatically at the Monitoring and data management center (MDMC) of UHS and the ANRS pharmacovigilance unit. Inserm-ANRS declares to the French National Commission of Informatic and Liberty (CNIL) that data management is compliant with the requirements of the modified Law n° 78-17 of January 6 1978 – Law 2018-493 - of June 20 2018 relative to information technology, files and civil liberties.

## **Monitoring**

Monitoring will be conducted according to the Good Clinical Practice (ICH Harmonized Tripartite Guidelines for Good Clinical Practice 1996) to guarantee the good quality of the research and safeguard the health and the rights of the patient.

### **1.1.3 On site**

The on-site trial activities (patient management; drug management and dispensation; trial monitoring) will be done under the responsibility of the head of project, based at the UHS in Phnom Penh. They will be responsible for coordinating all clinical activities for the trial:

- Recruitment, training and management of the clinical monitors;
- Organising and supporting clinical patient follow-up on site;
- Supervision of trial drug management;

- Member of the decision support committee;

On each investigational site, a physician known will have the medical responsibility to conduct the trial according to the protocol. They will be responsible, under the supervision of the head of project, in organizing the trial follow-up and management on site:

- Organisation of patient screening, enrollment and follow-up;
- Report clinical and biological data in the Case Report Form (CRF) according to the most updated SOP that will be provided;
- Report and document all Serious Adverse Events and sent follow-up report when necessary;
- Communication and coordination with the Decision Support Committee (DSC) and MDMC;
- Preparation and facilitation of the monitoring visit;

The clinical monitor must give the MDMC monitor access to relevant hospital or clinical records, to confirm their consistency with the CRF entries. No information about the identity of the subjects should appear on the CRF. The CRF must be completed within the week following the patient's visit. All CRF must be signed by the physician responsible of the patient follow-up. CRF will be considered as the source document for all the study sites regarding all the informations it contains.

#### **1.1.4 Monitoring activities**

**Monitoring activities will be coordinated by the coordination center. The trial monitors will visit the site regularly during the study:**

- Check the adherence to the protocol and to Good Clinical Practice (patient informed consent, protocol visit and blood test schedule...);
- Assist in the trial organisation and management on site (communication between collaborators, treatment or material availability, tracing laboratory samples follow-up and result in collaboration with the lab technician);
- Check the completeness and the accuracy of patient data on the CRF;
- Collect and check the Serious Adverse Events reporting, documentation and follow-up, and send the forms to the sponsor;
- Evaluate the progress of enrolment.

## **14. STATISTICAL ANALYSES**

### **Calculation of number of patients needed**

The study will be powered to detect an increase of HCV combined-testing uptake from 60% in the facility arm to 80% in the community arm among subjects older than 40 years.

According to Cambodia DHS report 2014, the average rural household size is 4 persons and the proportion of persons aged more than 40 years old is 25%, the cluster size is so estimated to 50.

The following assumptions and definitions will be used for the sample size calculation:

- an intra-class correlation of 0.01
- significance level  $\alpha = 0.05$
- power  $(1-\beta) = 80\%$
- clusters size: 50
- Design effect: 1.5

When accounting for the above-mentioned assumptions, 300 patients will need to be screened for HCV RNA and so, 6000 individuals aged above 40 years old will need to be screened by RDT (5% of patients are expected to have a positive HCV Ab). With an estimated median testing uptake of 60-70%, if we want to reach 6000 participants screened, it would be necessary to propose testing to 8000 participants from 160 clusters (80 clusters per intervention).

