**Expected enrolment**

8000 patients in 160 clusters located in 2 provinces (Kompong Cham and Siem Reap)

---

**Outcomes**                      **Primary outcome: combined-testing uptake** defined as the number of persons tested for HCV RDT AND HCV RNA and aware of their status among the total number of persons eligible residing in the region where the intervention takes place

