**Statistical methods**

---

The study will be powered to detect an increase of HCV combined-testing uptake from 60% in the facility arm to 80% in the community arm among subjects older than 40 years.

The following assumptions and definitions will be used for the sample size calculation:

- an intra-class correlation of 0.01
- significance level  $\alpha = 0.05$

- power  $(1-\beta) = 80\%$
- clusters size: 50 persons aged more than 40 years old
- Design effect: 1.5

When accounting for the above-mentioned assumptions, 300 patients will need to be screened for HCV RNA and so, 6000 individuals aged above 40 years old will need to be screened by RDT (5% of patients are expected to have a positive HCV Ab.). With an estimated median testing uptake of 60-70%, if we want to reach 6000 participants screened, it would be necessary to propose testing to 8000 participants from 160 clusters (80 clusters per intervention).

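### At the stated 60-70% uptake, offering testing to 8,000 people gives 4,800-5,600 tested and 240-280 antibody-positive, not 6,000 and 300; the planned yield needs 75% uptake

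*Protocol*

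**What the plan says.** Section 14 of the protocol (calculation of number of patients needed) sets out a chain of counts, and the statistical methods entry of the study summary repeats it.

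- Effect to detect: "an increase of HCV combined-testing uptake from 60% in the facility arm to 80% in the community arm", with "an intra-class correlation of 0.01", 5% significance, 80% power, clusters of 50 and a design effect of 1.5.
- Requirement: "300 patients will need to be screened for HCV RNA and so, 6000 individuals aged above 40 years old will need to be screened by" the rapid antibody test, because "5% of patients are expected to have a positive HCV Ab".
- Conversion to the number approached: "With an estimated median testing uptake of 60-70%, if we want to reach 6000 participants screened", then "it would be necessary to propose testing to 8000 participants from 160 clusters (80 clusters per intervention").

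The expected enrolment entry of the summary gives the same total as "8000 patients in 160 clusters located in 2 provinces". The inclusion criteria in section 6 require signed consent, at the latest when the RDT is done.

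**The concern.** The last step of the chain does not follow from its own inputs. Reaching 6,000 tests from 8,000 offers needs 75% uptake, above the top of the range given in the same sentence. No other uptake figure or allowance in the protocol links 6,000 to 8,000.

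The range also sits awkwardly beside the effect size. Section 7 gives antibody-testing uptake and combined-testing uptake the same denominator, and nobody can count for combined testing without an RDT. RDT uptake therefore cannot be lower than combined uptake in either arm.

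What is at stake is the yield that the design is said to deliver. Anyone who compares accrual with 6,000 tested and 300 RNA-tested would be using a target that the stated uptake does not support. Fewer positives found also means fewer cases available for linkage, treatment uptake and SVR12.

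**Working it through.** **Inputs**, all from section 14: 8,000 offered (160 clusters of 50, so 4,000 per arm); uptake 60-70%; antibody prevalence 5%; targets 6,000 RDT and 300 RNA; 60% versus 80%; two-sided 5% (sidedness is not stated, so this is an assumption); power 80%; design effect 1.5, which agrees with 1 + 49 × 0.01 = 1.49.

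**1. What reproduces.** 300 / 0.05 = 6,000, and 160 × 50 = 8,000. The link between the two does not reproduce: 6,000 / 8,000 = 0.75.

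**2. Yield from 8,000 offers** (tested = 8,000 × uptake; positive = tested × 0.05), and offers needed for 6,000 tests (6,000 / uptake, rounded up):

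| Uptake | Tested | Antibody-positive | Offers needed for 6,000 |
|---|---|---|---|
| 60% | 4,800 | 240 | 10,000 (200 clusters) |
| 65% | 5,200 | 260 | 9,231 (about 185 clusters) |
| 70% | 5,600 | 280 | 8,572 (about 172 clusters) |
| 75% | 6,000 | 300 | 8,000 (160 clusters) |

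Within the stated range, the shortfall is 400-1,200 tests (7-20% of 6,000) and 20-60 positives.

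**3. Fit with the hypothesis.** With equal arms, the minimum number tested by RDT is 0.60 × 4,000 + 0.80 × 4,000 = 2,400 + 3,200 = 5,600. That is 70% pooled uptake and 280 positives (120 + 160). This is a floor, because RDT uptake may exceed combined uptake. Of the stated range, only the top value, 70%, is compatible with the hypothesis. A value of 75% is also compatible: for illustration, RDT uptake of 65% and 85% averages 75%.

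**4. Effect on power, taking the plan's approach at face value** (RNA-tested people as the sample, design effect 1.5).

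Required n per arm = [1.96 × √(2 × 0.7 × 0.3) + 0.842 × √(0.24 + 0.16)]² / 0.20², which gives 82. Then 82 × 1.5 = 123 per arm, or 246 in total. With continuity correction it is 91 per arm, or 274 in total after the design effect. The stated 300 is above both.

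Power = Φ{[0.20 × √m − 1.96 × √0.42] / √0.40}, where m is the number per arm divided by 1.5:

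| RNA-tested, total | Power |
|---|---|
| 240 | 79.4% |
| 260 | 82.5% |
| 280 | 85.2% |
| 300 | 87.6% |

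With the 280 split as 120 and 160, power is 84.8%.

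**The case against.** Several points on the other side stand.

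- **The uptake range may be the loose item, not the 8,000.** The 8,000 also matches the sampling scheme in section 5: 8 areas × 10 villages × 100 households, at about one person over 40 per household (4 × 25%). The hypothesis allows 75% pooled uptake. The documents do not show which figure is wrong, so the correction should not presume that 60-70% is right.
- **The planning inputs are soft.** An antibody prevalence of 5.4% at 5,600 tested, or 6.25% at 4,800, would restore 300 positives. That is a fair comment on precision, but the protocol fixes 5%, and the sentence must agree with its own inputs.
- **The enrolment label is a wording matter.** Section 14 says plainly that testing is offered to 8,000. Even so, people who decline or do not attend never sign consent and so are not enrolled.

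Two stronger readings are tempting, and the documents support neither.

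The first is that the trial is underpowered and must approach 8,572-10,000 people. On the plan's own approach, power is 79-85% with 240-280 RNA-tested, against a target of 80%. Section 7 also defines the primary endpoint over all eligible residents, a denominator that low uptake does not shrink.

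The second is that the secondary comparisons lose their denominators. Active case detection is defined over eligible residents, and linkage over the estimated number with active infection in the area. For these two, lower uptake reduces the numerator, not the denominator. The protocol states no precision for secondary outcomes that would need recomputing.

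**Conclusion.** The inconsistency is real and needs no outside figure: the 60-70% uptake, the 8,000 offered and the 6,000 tested (with 300 RNA-tested) cannot all stand. At the stated uptake the plan overstates its yield by 400-1,200 RDT tests and 20-60 antibody-positives. Below 70%, the stated uptake also contradicts the 60%/80% hypothesis.

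The size rests on the protocol's own 5% prevalence, equal arms of 4,000, and the shared denominator of the two uptake endpoints in section 7. The power figures also assume a two-sided test and accept the plan's use of RNA-tested people as the sample; whether that suits the endpoint as defined is a separate question.

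The practical consequence is modest. The primary comparison suffers no material loss of power. The main effect is a smaller number of detected cases available for linkage, treatment uptake and SVR12. The text should be corrected, but the design does not have to change.

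**What to change.** Keep 8,000 offered and 160 clusters, and make uptake, number tested and number RNA-tested agree, in section 14 and in the summary. There are two ways:

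1. State pooled RDT uptake as about 75%, justify it and show that it is consistent with 60% and 80% combined uptake. The 6,000 and 300 then stand.
2. Keep 70%, the only value in the stated range that fits the hypothesis, and restate the expected yield as about 5,600 tested and 280 antibody-positive. Replace the requirement of 300 accordingly, noting about 85% power on the plan's approach. If uptake of only 60% is thought realistic, the yield is 4,800 and 240, and the 60%/80% hypothesis must be revised as well.

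In the expected enrolment entry, describe the 8,000 as persons offered testing and give the number expected to consent and be tested separately.

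The cost is a text correction in three places, with no additional participants or clusters. Under the second option, the stated counts become slightly less favourable.

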## 5. METHODOLOGY

### Study design

This is a two-arms cluster-randomized controlled trial, in which clusters are defined as a group of 50 households corresponding to the service population of the CHWs.

The study will be conducted in 2 different provinces.

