### Study overview

A facility-based testing intervention (group 1) will be compared to a community-based intervention (group 2). The study will be conducted in 2 separated provinces: Siem Reap and Kampong Cham provinces. Each province has approximatively one million of inhabitants and one

provincial hospital. Siem Reap province is composed of 4 ODs, 103 communes, 5 RHs and 88 HCs. Kampong Cham province is composed of 9 ODs, 107 communes, 9 RHs and 98 HCs.

For the study, one OD in Siem Reap province and 2 ODs in Kompong Cham province with approximately the same number of villages and inhabitants and the same distance from PHD will be selected. The districts are sub-divided into communes. Communes are further divided into villages. Villages are sub-divided into groups. A group is generally a combination of 50 households and one group will be defined as one cluster.

In order to decrease the risk of contamination between clusters, in each province, 4 geographic area, separated by communes not involved in the study, will be selected. A random selection of the geographic area in each province will be done to be part of arm 1 or 2.

**For each geographic area**, a multistage cluster sampling method will be used to select study participants:

1- A Probability proportional to size (PPS) sampling method to select 10 villages in each selected GA will be realized in a first step

2- Then, a preliminary mission will be organized in order to identify and confirm the location of HHs in the 10 selected villages. During this mission, information on age of inhabitants will be collected with the heads of village and a list of HHs will be identified

3- A Simple random sampling (SRS) method will be realized to select 100 households per village within the 10 selected villages

4- In each selected household, all persons aged more than 40 years old will be proposed to be part of the study.

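### The stated 80% power is worked out for 160 clusters of 50 and ends in a count of RNA-tested persons, but the protocol randomises 8 geographic areas and its primary endpoint divides by all eligible residents

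*Protocol*

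**What the plan says.** Section 14 (Calculation of number of patients needed), repeated under Statistical methods in Section 1, powers the trial for "an increase of HCV combined-testing uptake from 60% in the facility arm to 80% in the community arm among subjects older than 40 years". It assumes "an intra-class correlation of 0.01", a cluster size of 50, a design effect of 1.5, alpha 0.05 and 80% power. From these it states that "300 patients will need to be screened for HCV RNA". It then divides by an expected 5% antibody prevalence to reach 6,000 RDT-screened, and concludes that "it would be necessary to propose testing to 8000 participants from 160 clusters (80 clusters per intervention". The cluster size comes from the same section: 50 households, 4 persons per household, 25% aged over 40.

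Section 5 (Study design) says that "clusters are defined as a group of 50 households corresponding to the service population of the CHWs"; Section 1 gives the same definition.

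Study overview, also in Section 5, describes allocation differently: "in each province, 4 geographic area, separated by communes not involved in the study, will be selected", and these areas are then randomly assigned to arm 1 or arm 2. Within each area, 10 villages are drawn with probability proportional to size, and then "A Simple random sampling (SRS) method will be realized to select 100 households per village within the 10 selected villages". Section 15.1 confirms 8 geographic areas in all.

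Sections 7 and 14 define the primary endpoint as persons tested by RDT and by RNA, and aware of their status, over all eligible persons residing in the region.

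**The concern.** In a cluster trial, power depends on the number and size of the units that were randomised. Section 14 counts household groups. Under Section 5 these groups are not allocated to arms, and they are not sampled as units either, because 100 households are drawn at random across each village. The randomised unit is the area.

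The calculation also mixes populations. The cluster size of 50 counts all adults over 40. The resulting 300 counts persons who had an RNA test, which only RDT-positives receive. The endpoint's denominator is every eligible resident.

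The power statement is what the DSMB would work from when it advises on the number of subjects needed (Section 12.2). A declared count of 160 clusters also invites an analysis that treats the groups as independent units, which would overstate precision if areas differ.

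**Working it through.** **Reproducing the plan's figures.**
- Design effect: 1 + (50 − 1) × 0.01 = 1.49, the stated 1.5.
- 300 / 0.05 = 6,000, and 8,000 / 50 = 160. Also 8 areas × 10 villages × 2 nominal groups of 50 households = 160, so the 160 are subdivisions of the sample inside 8 areas.
- Two proportions, 60% v 80%, two-sided 0.05 (sidedness assumed), 80% power: 78.5 per arm with unpooled variance, 82 with pooled variance, 91 with continuity correction. In total, times 1.5: 2 × 78.5 × 1.5 = 235; 2 × 82 × 1.5 = 246; 91 × 1.5 = 136.5, rounded up to 137 per arm, 274. None gives 300. Conversely, 300 / (2 × 1.5) = 100 effective per arm, which has about 88% power.

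**Size of the randomised unit, from the protocol's own inputs.** 10 villages × 100 households × 4 persons × 25% = 1,000 eligible adults per area; 8 × 1,000 = 8,000. At ICC 0.01 the design effect is 1 + 999 × 0.01 = 10.99, against 1.49 for a group of 50.

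**Mismatch of populations.** Spread over 160 groups, 300 RDT-positives are 300 / 160 = 1.9 per group, so a design effect built on 50 per cluster does not belong to that count.

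**Power for the design as randomised.** Assumptions: 4 v 4 areas (Section 5 does not state an equal split); an area-level comparison adjusted for province, hence 8 − 3 = 5 df (6 df without province); every ICC other than 0.01; no extra correlation within villages. With m persons per area, DE = 1 + (m − 1) × ICC and

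SE = √[(0.6 × 0.4 + 0.8 × 0.2) × DE / (4m)] = √[0.40 × DE / (4m)].

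Power is taken from the noncentral t with noncentrality 0.20 / SE. For all eligible persons, m = 1,000; at ICC 0.01, SE = √(0.40 × 10.99 / 4,000) = 0.0332 and the noncentrality is 6.03.

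| Area-level ICC | DE | Power, 5 df | Power, 6 df |
|---|---|---|---|
| 0.01 (protocol's only ICC) | 10.99 | 99.7% | 99.8% |
| 0.02 (assumed) | 20.98 | 93% | 95% |
| 0.03 (assumed) | 30.97 | 82% | 85% |
| 0.05 (assumed) | 50.95 | 61% | 65% |
| 0.10 (assumed) | 100.9 | 37% | 39% |

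Power drops below 80% above an ICC of about 0.031 (5 df) or 0.034 (6 df).

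**The same design on the plan's own count.** 300 RDT-positives over 8 areas gives m = 37.5. At ICC 0.01, DE = 1.365, and power is 75.5% (5 df) or 78.8% (6 df).

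**Village correlation.** With 10 villages of about 100 eligible adults per area, DE = 1 + 99 × ICC(village) + 900 × ICC(area). If the two ICCs are equal this is 1 + 999 × ICC. With an assumed village ICC of 0.05 and area ICC of 0.03 it is 1 + 4.95 + 27 = 32.95, and power (5 df) is 79% rather than 82%.

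**The case against.** The best defence has four parts.

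First, the protocol does not hide the allocation: Section 5 states it, and Section 15 twice refers to 8 areas, so an attentive reader would not be misled. That is fair, but Section 5 also calls the 50-household group the cluster, and Section 14 gives 80 clusters per intervention. The document contradicts itself, and a separate statistical analysis plan would not remove a figure stated here.

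Second, a reader might infer that the trial is underpowered. The documents do not support that. On all eligible persons at the only ICC the protocol gives, power exceeds 99%. The lower figures need area-level ICCs that are assumptions, or the RDT-positive count, where the gap from 80% is small. The 4 v 4 split and the 5 df are assumptions too.

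Third, a reader might infer that the calculation used a normal critical value and ignored the small number of units. Section 14 shows no formula or test, and the usual formulae do not return 300, so the method is unknown and no such claim can be made.

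Fourth, restating power on all eligible persons presupposes what counts as a success. This stands. Only RDT-positives, about 5%, receive an RNA test, so on the literal endpoint wording uptake among all eligible persons could not reach 60% or 80%. Those targets make sense only if an RDT-negative person who knows the result counts as a success, which the protocol does not say. The fix has to settle this first.

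**Conclusion.** The point holds as a mismatch of unit and denominator. The 80% power is calculated for clusters that are not randomised and ends in a count that is not the endpoint's denominator; that count is also not reproduced by the stated inputs. The 80% is therefore not derived for this design or this endpoint.

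What the design does deliver depends on a quantity the protocol does not give, the area-level ICC, and the 80% mark is crossed at about 0.031 to 0.034. No shortfall on all eligible persons is shown. The table rests on 4 areas per arm, an area-level test with 5 or 6 df, RDT-negatives aware of their result counting as successes, and no additional village correlation. The statement needs correcting because it misidentifies the unit on which the primary comparison rests; it is not a ground for changing the number approached.

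**What to change.** 1. In the Methodology line of Section 1, in Section 5 and in Section 14, name the geographic area as the randomised cluster (8 in all, with the split per arm stated). Describe villages and households as sampling stages.
2. In the primary endpoint, state that an RDT-negative person who is aware of the result counts as a success.
3. Replace the power paragraph in Section 14 and its copy in Section 1. Give power for 60% v 80% of all eligible persons in 8 areas of about 1,000, over a range of area-level ICCs labelled as assumed, with DE = 1 + 99 × ICC(village) + 900 × ICC(area). State the test and its degrees of freedom.
4. Give the RDT-positive count only as the expected precision for secondary outcomes. At the protocol's 60–70% uptake and 5% prevalence, 8,000 × 0.60 × 0.05 = 240 to 8,000 × 0.70 × 0.05 = 280.
5. Keep 8,000 and report power as conditional on the area-level ICC. Approaching more people in the same areas would gain little: at ICC 0.05, DE / m is already 50.95 / 1,000 = 0.051, against a limit of 0.05.

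The cost is a rewrite of one section, with matching edits to the cluster definition and the endpoint. No extra participants are needed, but the unconditional 80% claim is given up.
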